## LIST OF ABBREVIATIONS AND RELEVANT DEFINITIONS

|                |                                                                                                                                                                                                                                                                                                                                                  |
|----------------|--------------------------------------------------------------------------------------------------------------------------------------------------------------------------------------------------------------------------------------------------------------------------------------------------------------------------------------------------|
| ABR     | ABR form, General Assessment and Registration form, is the application form that is required for submission to the accredited Ethics Committee (In Dutch, ABR = Algemene Beoordeling en Registratie)                                                                                                                                      |
| AE      | Adverse Event                                                                                                                                                                                                                                                                                                                             |
| AR      | Adverse Reaction                                                                                                                                                                                                                                                                                                                          |
| CA      | Competent Authority                                                                                                                                                                                                                                                                                                                       |
| CCMO    | Central Committee on Research Involving Human Subjects; in Dutch: Centrale Commissie Mensgebonden Onderzoek                                                                                                                                                                                                                               |
| CV      | Curriculum Vitae                                                                                                                                                                                                                                                                                                                          |
| DSMB    | Data Safety Monitoring Board                                                                                                                                                                                                                                                                                                              |
| EU      | European Union                                                                                                                                                                                                                                                                                                                            |
| EudraCT | European drug regulatory affairs Clinical Trials                                                                                                                                                                                                                                                                                          |
| GCP     | Good Clinical Practice                                                                                                                                                                                                                                                                                                                    |
| IB      | Investigator's Brochure                                                                                                                                                                                                                                                                                                                   |
| IC      | Informed Consent                                                                                                                                                                                                                                                                                                                          |
| IMP     | Investigational Medicinal Product                                                                                                                                                                                                                                                                                                         |
| IMPD    | Investigational Medicinal Product Dossier                                                                                                                                                                                                                                                                                                 |
| METC    | Medical research ethics committee (MREC); in Dutch: medisch ethische toetsing commissie (METC)                                                                                                                                                                                                                                            |
| (S)AE   | (Serious) Adverse Event                                                                                                                                                                                                                                                                                                                   |
| SPC     | Summary of Product Characteristics (in Dutch: officiële productinformatie IB1-tekst)                                                                                                                                                                                                                                                      |
| Sponsor | The sponsor is the party that commissions the organisation or performance of the research, for example a pharmaceutical company, academic hospital, scientific organisation or investigator. A party that provides funding for a study but does not commission it is not regarded as the sponsor, but referred to as a subsidising party. |
| SUSAR   | Suspected Unexpected Serious Adverse Reaction                                                                                                                                                                                                                                                                                             |
| Wbp     | Personal Data Protection Act (in Dutch: Wet Bescherming Persoonsgegevens)                                                                                                                                                                                                                                                                 |
| WMO     | Medical Research Involving Human Subjects Act (in Dutch: Wet Medisch-wetenschappelijk Onderzoek met Mensen)                                                                                                                                                                                                                               |

## SUMMARY

**Rationale:** The quality of hospital-based care for patients with palliative care needs is still suboptimal. Identification of palliative care needs and timely discussion of the patients' wishes and preferences often not take place. It was stated by the SONCOS working group, that from 2017 on, hospitals need to have a palliative care team available. Studies suggest that when a GP is coordinator of palliative care of a patient, unwanted hospitalizations may be prevented. Transitional palliative care teams (based in the hospital, with a GP and/or home care services in the team) might therefore be the solution. The OLVG has such a transitional team and the current study aims to explore the work of this team

**Objectives:**

- To explore reasons of hospitalizations of patients for whom a palliative team was consulted in the hospital;
- To explore why, when and by whom the palliative team was consulted;
- To explore needs and expectations of the patient with regard to the palliative care team;
- To investigate whether agreements with and wishes of patients (with regard to hospitalizations, treatments and preferred place of death) are fulfilled after they had a consultation from the palliative care team;
- To investigate prognoses estimated by nurse specialist with actual time to death;
- To explore communication between the palliative care team and GPs and home care/care homes;
- To explore which % of consultations is financed and what are reasons for not financing a consult (according to DBC- registrations)

**Study design:** Retrospective study

**Study population:** adults, treated in the OLVG hospital, consultation by the palliative care team.

**Main study parameters/endpoints:**

Reason for hospitalization

**Nature and extent of the burden and risks associated with participation, benefit and group**

**relatedness:** There is no burden for the patient as this is a retrospective study design.

## **1. INTRODUCTION AND RATIONALE**

The quality of hospital-based care for patients with palliative care needs is still suboptimal.

Identification of patients with palliative care needs and end-of-life-preference discussions often do not take place (1, 2). Furthermore, there is no clear plan for the treatment of symptoms when the patient is at home. This may result in undesirable unplanned hospital readmissions in the last phase of life (3). Also, certain procedures (such as ascites paracentesis) may well be performed in primary care by a trained doctor, however when trained doctors are not available, the patient will be admitted to the hospital for this procedure.

Currently, an increasing number of hospitals form a palliative care team. The Dutch foundation for oncology collaboration (SONCOS) even added this as a requirement for cancer centres, becoming effective from January 1st, 2017 on. With these norms, hospitals are required to have a multidisciplinary palliative team that measures patients' palliative care need and is accessible for consultation. The goals of these palliative teams are twofold: to improve quality of intramural palliative care and to improve communication and collaboration with primary care (4).

There is evidence that the number of people who die in the hospital and the number of transfers in the last three months of life are lower when a GP is the main coordinator of (palliative) care and if there are sufficient resources in primary care (5). Therefore, expanding the hospital-based team to a transitional palliative care team that consists not only of hospital professionals, but also professionals working in primary care (GP and community care nurse, both specialized in palliative care) might help tackle the described issues.

The OLVG hospital in Amsterdam currently has a transitional palliative care team and the number of consultations is rapidly increasing over the years. Approximately 75% of the consults takes place during hospitalization and the rest in the outpatient department. Their structured approach to the wishes and preferences of the patient as their primary priority, and good communication with the GP is an ideal example for hospital based transitional palliative care teams. The OLVG has such a transitional team and the current study aims to explore the work of this team.

## **2. OBJECTIVES**

In this exploratory study, we will investigate opportunities and threats of a (transitional) palliative care team. Objectives:

- To explore reasons of hospitalizations of patients for whom a palliative team was consulted in the hospital;
- To explore why, when and by whom the palliative team was consulted;
- To explore needs and expectations of the patient with regard to the palliative care team;
- To investigate whether agreements with and wishes of patients (with regard to hospitalizations, treatments and preferred place of death) are fulfilled after they had a consultation from the palliative care team;
- To investigate prognoses estimated by nurse specialist with actual time to death;

- To explore communication between the palliative care team and GPs and home care/care homes;
- To explore which % of consultations is financed and what are reasons for not financing a consult (according to DBC- registrations)

### 3. STUDY DESIGN

Retrospective analyses of patients with a palliative care team consultation between January and May 2016 in the OLVG location East.

We will analyze data on the period of the consultation itself, 6 months prior to first consultation (prior hospitalizations and disease history) and 6 months after first consultation (follow up).

*Timeline (recruitment of new consults of the palliative care team between January and May 2016)*

[figure not shown]

### 4. STUDY POPULATION

#### 4.1 Population (base)

Patients of whom the palliative care team was consulted for the first time between January and May 2016 with a complete consultation of the palliative care team

#### 4.2 Inclusion criteria

In order to be eligible to participate in this study, a subject must meet all of the following criteria:

- Adult ( $\geq 18$  years)
- Consulted by the palliative care team

#### 4.3 Exclusion criteria

A potential subject who meets any of the following criteria will be excluded from participation in this study:

- Incomplete consult without discussion in multidisciplinary meeting

#### **4.4 Sample size calculation**

Due to the exploratory nature of this study, a sample size calculation is not possible. In our opinion, a sample of 50-60 patients will be sufficient to explore the objectives of this study. With 175 complete consultations in 2015, inclusion of patients in the first 4 months of 2016 will result in a sample between 50-60 patients.

### **5. TREATMENT OF SUBJECTS**

NA

### **6. INVESTIGATIONAL PRODUCT**

NA

### **7. NON-INVESTIGATIONAL PRODUCT**

NA

### **8. METHODS**

Objectives:

- To explore reasons of hospitalizations of patients for whom a palliative team was consulted in the hospital;
- To explore why, when and by whom the palliative team was consulted;
- To explore needs and expectations of the patient with regard to the palliative care team;
- To investigate whether agreements with and wishes of patients (with regard to hospitalizations, treatments and preferred place of death) are fulfilled after they had a consultation from the palliative care team;
- To investigate prognoses estimated by nurse specialist with actual time to death;
- To explore communication between the palliative care team and GPs and home care/care homes;
- To explore which % of consultations is financed and what are reasons for not financing a consult (according to DBC- registrations)

#### **8.1 Study parameters/endpoints**

##### **Endpoints**

- Reasons for hospitalization of patients for whom a palliative team was consulted during hospitalization. With use of an expert panel, we will discuss preventability of these hospitalizations in the analysis phase of the study.
- Timing & reasons for palliative team consultation & profession of person who consulted the palliative care team
- Needs and expectations of patients with regard to palliative care team consultation

- Fulfilment of agreements with and wishes of patients (with regard to hospitalizations, treatments and preferred place of death)
  - o Agreements available/wishes noted during consults with palliative care team regarding future hospitalizations, treatments and preferred place of death
  - o Agreements and wishes fulfilled 6 months after consultation?
- Estimated prognosis by nurse specialist and actual time to death
- communication of the palliative care team with GPs and home care/carehomes:
  - o Timing & amount of communication
  - o Oral/written communication
  - o Content of handover
- Financing of consultations and reasons for not financing a consult (according to DBC-registrations)

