## 8.2 Randomisation, blinding and treatment allocation

NA

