|--|----------------------------------------------------------------------------------------------------------------------------------------------------------------------------------------------------------------------------------------------------------------------------------------------------------------------------------------------------------------------------------------------------------------------------------------------------|--------------------------------------------------------------------------|
|  | hospitalization
- Wishes and expectations of the patient with regard to the palliative care team
- Agreements/wishes of patients noted with regard to hospitalization/ treatment / preferred place of dying
- Prognosis (estimated by nurse specialist)
- Contact between PT and GP/home care/care home: number of contacts, method, handover
For inpatient clinic:
- Hospitalization department
- Reason for hospitalization | - Date and place of death
- DBC financing: DBC registered & approved? |
|--|----------------------------------------------------------------------------------------------------------------------------------------------------------------------------------------------------------------------------------------------------------------------------------------------------------------------------------------------------------------------------------------------------------------------------------------------------|--------------------------------------------------------------------------|

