## 10. STATISTICAL ANALYSIS

Descriptive statistics (mean±SD, median (IQR) or count (%)) will be used to describe the study sample with regard to all outcomes.

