**11.4 Benefits and risks assessment, group relatedness**

This study will give insight into the work of the palliative care team. A report with results will be send to the palliative care team and hospital directors in order to improve the work of the team.

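### Preventability of the index admissions rests on an expert-panel discussion in the analysis phase, with no independent ratings beforehand and nothing that keeps later outcomes from the panel

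*Protocol*

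**What the plan says.** The Summary names one main study parameter: "Reason for hospitalization". Section 8.1 lists the same item first among the endpoints, for patients seen by the team during an admission, and attaches a judgement to it: "With use of an expert panel, we will discuss preventability of these hospitalizations in the analysis phase of the study".

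The protocol adds nothing more on how this judgement is made. It gives no definition or scale of preventability, panel size or composition, rating step before discussion, rule for disagreement, or limit on the case material.

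Three other places bear on the point:

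- Section 3 sets a retrospective design with six months of follow-up after the first consultation. The follow-up column of the table in section 8.3 lists hospitalizations, emergency department visits and "Date and place of death".
- Section 10 states that descriptive statistics "will be used to describe the study sample with regard to all outcomes". It offers mean, median or count.
- Section 11.4 says of the results: "A report with results will be send to the palliative care team and hospital directors in order to improve the work of the team".

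**The concern.** Whether an admission could have been prevented is a question about what was known and available when the patient was admitted. Later hospitalizations and the date and place of death all come after that decision. A panel that knows them may judge the admission differently from one that does not. The protocol places the judgement at the stage when this information is on file and does not keep the two apart.

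The second issue is reproducibility. Preventability is a matter of opinion, and experts can differ. If members only discuss, the product is one group judgement per admission. How far members differed beforehand, and whether a few members carried the rest, cannot then be seen.

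At stake is the credibility of whatever the report says about preventability. The rationale in section 1 is partly about undesirable readmissions and about procedures that might be done in primary care. Statements on preventability are therefore likely to interest the report's readers. The study tests no hypothesis, so type I error and power are not involved.

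**Working it through.** **1. What is fixed, set side by side.**

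| Element | Protocol |
|---|---|
| Who judges | An expert panel (8.1) |
| How | By discussion (8.1) |
| When | Analysis phase (8.1) |
| On file by then | Six-month hospitalizations, emergency visits, date and place of death (8.3) |
| Independent ratings first | Not stated |
| Later outcomes withheld | Not stated |
| Statistics | Descriptive only (10) |

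An agreement statistic could be named in a separate analysis plan, so its absence from section 10 is not the point. The point is how the data are generated. Agreement can be computed only from ratings made independently before discussion. If section 8.1 is followed as written and no such ratings are collected, they do not exist afterwards.

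**2. Number of admissions for the panel.** Inputs: 175 complete consultations in 2015, four months of inclusion and an expected 50 to 60 patients (section 4.4); about 75% of consults during hospitalization (section 1).

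- The protocol's own figure: 175 × 4/12 = 58.3, which lies inside 50 to 60 and so reproduces.
- Index admissions: 0.75 × 50 = 37.5 and 0.75 × 60 = 45, so about 38 to 45. At 58.3 patients, 0.75 × 58.3 = 43.75, or about 44.

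The 75% refers to consults; applying it to first-consulted patients is an assumption.

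**3. How much disagreement a discussion could conceal (illustration only).** Assume two raters, a yes/no scale and the same share p rated preventable by each. The protocol gives none of these, nor any value of p or kappa (κ). Expected disagreement is 2p(1 − p)(1 − κ).

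| p (assumed) | κ = 0.4 | κ = 0.6 |
|---|---|---|
| 0.1 | 2 × 0.1 × 0.9 × 0.6 = 0.108 | 2 × 0.1 × 0.9 × 0.4 = 0.072 |
| 0.3 | 2 × 0.3 × 0.7 × 0.6 = 0.252 | 2 × 0.3 × 0.7 × 0.4 = 0.168 |
| 0.5 | 2 × 0.5 × 0.5 × 0.6 = 0.300 | 2 × 0.5 × 0.5 × 0.4 = 0.200 |

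At p = 0.3 and 44 admissions this is 0.252 × 44 = 11.1 or 0.168 × 44 = 7.4 discordant cases, against 0.3 × 44 = 13.2 rated preventable by each rater.

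**4. What could be learned after the fix.** The large-sample (Fleiss-Cohen-Everitt) standard error of kappa, with two raters, equal marginals and 44 admissions, gives these 95% CI half-widths at a true kappa of 0.6: about 0.40, 0.27 and 0.24 with 10%, 25% and 50% preventable. Over kappa 0.4 to 0.8 and 10 to 50% preventable, the range is about 0.18 to 0.44. Agreement could be estimated, but only coarsely.

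**The case against.** The strongest reply is that this argues from silence. The scale, case material, independent ratings and agreement statistic are often set out in an analysis plan or a panel procedure. The wording of section 8.1 does not exclude any of them. In a retrospective chart study the outcomes already exist whenever the rating is made, so the timing alone is no fault. Preventability is also not among the seven listed objectives, and the study is exploratory.

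Much of this stands, and it rules out several stronger readings that a reader might infer:

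- *That the panel will judge with the outcomes in view.* The protocol does not say what the panel is shown. The NA under "Randomisation, blinding and treatment allocation" is natural in a study without randomised treatment and is not a decision to reveal outcomes.
- *That open discussion will settle a preventable percentage.* The text says preventability will be discussed and promises no percentage. Section 11.4 speaks of results in general and does not mention preventability.
- *That hindsight would push judgements towards preventable.* Nothing in the protocol supports a direction. Early death could equally make an admission look unavoidable.
- *That the figures above measure hindsight bias.* They show only rater disagreement under assumed values.

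The reply does not remove the remaining point. Section 8.1 does state a method, and that method, followed as written, produces no independent ratings. An analysis plan can add a statistic, but it cannot create ratings that were never collected. The same panel can provide them in the same phase at little cost.

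**Conclusion.** The point holds as an inexpensive improvement to a stated method. It is not an error in a figure and not a demonstrated bias. Section 8.1 fixes a panel discussion in the analysis phase; the protocol neither withholds later outcomes from the panel nor asks for independent ratings first. As written, any statement on preventability would come without evidence of its reproducibility.

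The judgement concerns about 38 to 45 admissions, on the protocol's expected 50 to 60 patients and its approximate 75% inpatient share. The possible hidden disagreement is about 17 to 25% of admissions if 30% are preventable and kappa is 0.4 to 0.6, or about 7 to 30% if the share runs from 10 to 50%. These shares, the kappas, the two raters and the yes/no scale are assumptions. The size and direction of any effect of hindsight cannot be derived from the protocol.

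**What to change.** Amend the preventability sentence in section 8.1 to state that:

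1. before any discussion, each panel member independently rates each index admission on a preset scale;
2. the rating is made from a summary that withholds later follow-up and the date and place of death;
3. discussion is kept for discordant cases;
4. pre-discussion agreement is reported and, if a share judged preventable is reported, its final value is given with a 95% CI.

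This must be in place before the panel meets, because ratings made after discussion are no longer independent.

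The panel and the study phase stay the same. The cost is about 38 to 45 short summaries and one rating form. The agreement estimate will be imprecise at this sample size and should be presented as such.
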